## Abstract

Opioid Use Disorder (OUD) is a pervasive and devastating public health crisis that continues to take a heavy toll on individuals and communities across the United States. In 2021, approximately 473,000 veterans misused opioids in the past year. In the context of their military service and post-service life, Veterans with OUD often encounter unique barriers to recovery, including the reintegration into civilian society and the pursuit of stable, meaningful employment. The path to recovery from OUD is inextricably linked to the restoration of a stable and purposeful life, a fact underscored by the interplay of substance use, mental health, and employment outcomes. These factors necessitate a comprehensive approach to treatment that extends beyond mere pharmacological interventions. One such approach is Individual Placement and Support (IPS), a well-established evidence-based practice that focuses on supporting individuals with severe mental illness in their pursuit of competitive employment. The primary objective of this manuscript is to describe a two-arm, multi-site RCT designed to rigorously evaluate the efficacy of IPS when provided to veterans with OUD and provide the baseline demographics and characteristics of the participants who have enrolled to date. The central hypothesis guiding this research is that IPS can significantly improve vocational, psychosocial, and treatment outcomes of veterans in recovery from OUD, ultimately leading to a more successful reintegration into civilian life. Our study is timely as the VA has expanded IPS services to veterans with SUD this past year. Thus, this study is one of the first to examine IPS in a subpopulation of veterans with a SUD and may provide actionable data to support sustainment of IPS with this population.

## Introduction

Opioid Use Disorder (OUD) is a pervasive and devastating public health crisis that continues to take a heavy toll on individuals and communities across the United States. In 2017, the US. Department of Health and Human Services (HHS) declared the opioid crisis a public health emergency [1]. Over 9.2 million people in the US. misuse opioids [2]. The impact of this crisis is acutely felt within the veteran population, where the prevalence of OUD and its associated complications remains a formidable challenge. In 2021, approximately 473,000 veterans misused opioids in the past year [2]. In the context of their military service and post-service life, veterans with OUD often encounter unique barriers to recovery [3], including the reintegration into civilian society and the pursuit of stable, meaningful employment.

The path to recovery from OUD is inextricably linked to the restoration of a stable and purposeful life, a fact underscored by the interplay of substance use, mental health, and employment outcomes [4–6]. These factors necessitate a comprehensive approach to treatment that extends beyond pharmacological interventions. One such approach is Individual Placement and Support (IPS) [7], a well-established evidence-based practice that focuses on supporting individuals with severe mental illness in their pursuit of competitive employment [8, 9].

IPS emphasizes the principles of rapid job placement, personalized job development, ongoing job support, and a “place-then-train” philosophy [10]. IPS is a manualized approach with a validated treatment fidelity scale [11]. While IPS has demonstrated its effectiveness in improving employment outcomes among individuals with severe mental illness [8, 9], and among veterans with PTSD [12, 13] and broad-spectrum psychiatric disabilities [14], its applicability and efficacy in the unique context of veterans with OUD remain largely unexplored. The confluence of substance use and employment challenges makes this population a particularly challenging and, at the same time, vital target for intervention research.

Harrison and colleagues conducted a systematic review of IPS for persons with substance use disorders (SUD) [15]. Their results yielded five randomized controlled trials (RCTs) and two studies that were non-randomized controlled trials [16–20]. Of the RCTs, only one included a specific sample with OUD as opposed to other types of SUD [16]. The other six studies evaluated IPS among samples with co-occurring mental illness and SUD [17–20]. Those with OUD specifically were not reported or separated in analyses from other SUDs. Nonetheless, across all of the RCTs, IPS participants had better employment outcomes than control groups. Of note, two of the RCTs were with a veteran sample [18, 20]. Among the two non-randomized IPS studies, participants obtained employment at higher rates of employment than the general rate of employment for individuals with co-occurring SUD within the state the study was conducted in [21]. Results of the non-randomized study showed that IPS participants with and without SUD obtained competitive employment at similar rates [22].

Lones and colleagues evaluated the efficacy of IPS for 45 patients with OUD enrolled in a methadone treatment program [16]. This is the only study found to evaluate IPS among an OUD population. Participants were randomized to either receive a 6-month IPS intervention or to a waitlist. During the 6-month intervention period, half of the IPS group attained competitive employment compared to only 5% among the waitlist control, which increased to 22% after 12-months but stayed at 50% for the IPS group.

The primary objective of this manuscript is to describe a two-arm, multi-site RCT designed to rigorously evaluate the efficacy of IPS when provided to veterans with OUD and provide the baseline demographics and characteristics of the participants who have enrolled to date. The central hypothesis guiding this research is that IPS can significantly improve vocational, psychosocial, and treatment outcomes of veterans in recovery from OUD, ultimately leading to a more successful reintegration into civilian life. Our study is timely as the VA has expanded IPS services to veterans with SUD this past year. Thus, this study is one of the first to examine IPS in a subpopulation of veterans with a SUD and may provide actionable data to support sustainment of IPS with this population. Our study could improve our understanding of vocational rehabilitation needs, employment challenges and solutions, and relapse prevention for veterans with OUD.

## Methods

### Ethics approval and consent

This study is approved by the Institutional Review Boards of the Tuscaloosa VA Medical Center, The Birmingham VA Health Care System, and The University of Alabamain accordance with the Declaration of Helsinki. Written informed consent is obtained prior to participating in any study procedures. The study is monitored by an independent Data and Safety Monitoring Board and has a Certificate of Confidentiality approved by the National Institutes of Health.

### Overview of design, aims, and hypotheses

The purpose of this study is to evaluate the efficacy of IPS provided to veterans with OUD using a mixed methods approach. Our first aim is to conduct a prospective, multi-site, RCT to determine the efficacy of IPS compared to treatment-as-usual non-IPS vocational rehabilitation (non-IPS-VR). Consenting and eligible veterans who are currently unemployed or under-employed and are in treatment for OUD are randomized to either IPS or non-IPS-VR. Each participant receives IPS or non-IPS-VR and have outcomes assessed for 18 months. We hypothesize that participants who receive IPS will have significantly more weeks worked in a competitive job over 18 months compared to non-IPS-VR services. We also hypothesize that compared to non-IPS-VR, IPS recipients will earn significantly more income from competitive jobs and be significantly more likely to achieve steady employment, defined as working in a competitive job for 50% of the 18-month period. Our second aim is to explore and identify contextual barriers and facilitators of implementing rehabilitation services in both study arms and to achieving competitive employment among veterans with OUD. We will evaluate the implementation and employment challenges, optimal functioning, and OUD treatment adherence. We are employing a community-based participatory research (CBPR) approach to achieve this aim. True to CBPR approach, the interview guide for the present study was developed through an iterative interview process with various stakeholders, including employers of individuals with OUD, IPS and vocational rehabilitation specialists, Veterans, and researchers with expertise in this field. These various stakeholders were asked to identify various contextual barriers and facilitators of employment for Veterans with OUD. From these interviews, various overarching themes were developed to guide the development of the interview guide to further explore Veterans perspectives in the current study. The fundings of the barriers and facilitators will be published in a separate manuscript. For this study, we are also utilizing an iterative process of qualitative individual interviews with veterans with OUD that were randomized to IPS or non-IPS-VR. Our final aim is to evaluate the impact of IPS compared to non-IPS-VR on adherence to medications for OUD (MOUD) and rates of OUD relapse. We hypothesize that compared to non-IPS-VR, veterans who receive IPS will be significantly more likely to adhere to MOUD (i.e., those on MOUD only) and to have lower rates of OUD relapse.

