
### Eligibility criteria

Eligible participants are (1) consenting US. military veterans who are ≥ 19 years of age; (2) currently unemployed or underemployed (i.e., working < 20 h/week in competitive employment, or currently employed in a job that is not meaningful or well-matched to the veteran); (3) desiring to work in a competitive job; and (4) have a history of current or lifetime OUD according to DSM-5. Veterans with a history of traumatic brain injury may be included as long as they do not have a severe cognitive disorder. The key to attaining and sustaining employment in the context of a recovery model is being recognized for the potential contributions one has made in the past and can once again address moving forward. Eligible veterans are either unemployed, marginally employed, or caught in the trap of working in entry level jobs unrelated to their past education, training and/or military experience. The absence of work or career choices with relevance or meaning to the veteran’s life can be a determinant of accepting and sustaining treatment adherence. Meaningful work is often described as employment in a valued environment or performing work tasks related to one’s personal preferences or life experiences, military or non-military.

Exclusion criteria include (1) a current diagnosis of schizophrenia, schizoaffective disorder or other psychotic disorders; (2) diagnosis of dementia or severe cognitive disorder; (3) presence of current severe and unstable medical condition or terminal illness, that would contraindicate study participation or expose them to an undue risk; (4) unlikely that participant can complete the study, e.g., expected deployment, incarceration, long-term hospitalization, or relocation from the vicinity; (5) active suicidal or homicidal ideation making it unsafe for the participant to be included; or (6) current participation in another vocational interventional trial.

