### Recruitment procedures

Participants are recruited from the Tuscaloosa VA Medical Center and the Birmingham VA Health Care System as they naturalistically present for treatment in vocational rehabilitation services, residential treatment program, outpatient mental health clinics, and addiction recovery programs, are referred to the study, respond to the IRB-approved advertisement/letter, or make personal inquiry into the study. During the 3-year enrollment period, we plan for at least 180 veterans to be directly offered consent, 140 to sign consent, 120 to be randomized, and 100 veterans to complete the study at the two sites. Participants are modestly compensated for each baseline and the bimonthly assessment visits.

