### Individual placement and support intervention

IPS is a manualized model of supported employment that focuses on obtaining and maintaining competitive employment that align with the participants’ skills, abilities, knowledge, career interests, and prevocational training [34]. The IPS model encompasses eight principles: (1) *Competitive Employment:* The IPS intervention assists participants to directly engage in a competitive job rather than prevocational training or set-aside sheltered jobs. (*2) Systematic Job Development:* IPS specialists build an employer network based on participant’s interests, developing relationships with local employers by making systematic contacts. (3) *Rapid Job Search:* IPS specialists use a rapid job search approach to help participants obtain employment as soon as possible, rather than providing lengthy pre-employment assessment, training, and counseling. (4) *Integrated Services:* The IPS intervention is closely integrated with the treatment team, in this case the outpatient substance use treatment or MOUD program. (5) *Benefits Counseling:* IPS specialists help veterans obtain personalized, understandable, and accurate information about their VA, Social Security, Medicaid, and other government entitlements. (6) *Zero Exclusion:* IPS embraces the notion of “zero exclusion” criteria, i.e., does not preclude participants because of level of disability, work history, or active substance use. (7) *Time-Unlimited Support*: IPS follow-along vocational supports are continued for as long as the participant wants and needs the support (in this case for 18-months due to the time limits of the study). The unlimited support provides help during job transitions if the first job is not the preferred or best-matched job. (8) *Worker Preferences:* The IPS intervention is based on the participant's preferences and choices rather than the IPS specialist’s or treatment team’s judgements. The caseload size for an IPS Specialist is 20–25 clients. The IPS specialists provides all phases of employment services such as intake, assessment, job development, and job coaching.

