## Results

Since January 2023, 41 participants have been enrolled and randomized with 25 participants randomized to IPS (10 to site one, 15 to site two) and 16 to non-IPS-VR (3 to site one, 13 to site two). Enrollment will remain open until we achieve our enrollment threshold, no later than August 2025. Tables 1, 2 and 3 describe the baseline and clinical characteristics of the sample to date. To provide a contextual understanding of the study sample, we provide two study vignettes describing two cases, one from each study arm, as shown in Vignettes #1 and #2. Since enrollment and follow-up are still ongoing, no outcomes are presented in this report.

**Table 1 Tab1:** Baseline Demographics and Military History

Variable	IPS (*N* = 25)		Non-IPS-VR (*N* = 16)		Total (*N* = 41)	
	*M*	*SD*	*M*	*SD*	*M*	*SD*
Age (years)	44.4	10	54	11.26	48.2	11.4
Prior-Year Annual Income ($US)	$34,480	$25,587	$16,383	$14,990	$16,383	$14,990
	Frequency	Percent	Frequency	Percent	Frequency	Percent
Sex						
Male	21	84.0	14	87.5	35	85.4
Female	4	16.0	2	12.5	6	14.6
Race						
White	14	56.0	6	37.5	20	48.8
Black or African American	8	32.0	9	56.3	17	41.5
Asian, Mixed, or Other	3	12.0	1	6.3	4	9.8
Ethnicity						
Not Hispanic or Latino	25	100	16	100	41	100
Marital Status						
Single	7	28.0	4	25.0	11	26.8
Married	3	12.0	2	12.5	5	12.2
Divorced	13	52.0	7	43.8	20	48.8
Other	2	8.0	3	18.8	5	12.2
Education						
Less than High School Diploma	1	4.0	–	–	1	2.4
High School Diploma/GED	8	32.0	3	18.8	11	26.8
Vocational Training	11	44.0	11	68.8	22	53.7
Associate or Bachelor’s Degree	5	20.0	2	12.5	7	17.1
Branch of Service						
Army	11	44.0	10	62.5	21	51.2
Navy	9	36.0	2	12.5	11	26.8
Air Force	3	12.0	3	18.8	6	14.6
Other	2	8.0	1	6.3	3	7.3
Period of Service						
Vietnam Conflict	–	–	1	6.3	1	2.4
MAY-1975 to JUL-1990	5	20.0	8	50	13	31.7
Aug-1990 to APR-1991 Gulf War	2	8.0	3	18.8	5	12.2
MAR-1991 to AUG-2001	6	24.0	2	12.5	8	19.5
SEP-2001 to DEC-2010 OIF/OIF	12	48.0	6	37.5	18	43.9
2011 to present	7	28.0	–	–	7	17.1
Combat Exposure						
Served in Combat Zone	14	56.0	7	43.8	21	51.2

*M* Mean, *SD* Standard Deviation, *OIF* Operation Iraqi Freedom, *OEF* Operation Enduring Freedom

**Table 2 Tab2:** Baseline Disability Status, Work History, Number of Dependents, and Housing

Variable	IPS (*N* = 25)		Non-IPS-VR (*N* = 16)		Total (*N* = 41)	
	Frequency	Percent	Frequency	Percent	Frequency	Percent
SSI/SSDI						
Yes	5	20.0	8	50.0	13	31.7
No	20	80.0	8	50.0	28	68.3
Filing for SSI/SSDI	3	12.0	1	6.3	4	9.8

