VA Service-Connected Disability Status						
None	10	40.0	6	37.5	16	39.0
Filing for the first time	2	8.0	1	6.3	3	7.3
Filing for appeal	–	–	1	6.3	1	2.4
Receiving any SC disability	10	40.0	8	50.0	18	43.9
Filing for increase	3	12.0	–	–	3	7.3
Receiving 100% SC	6	24.0	3	18.8	9	22.0
Employment Status						
Unemployed	21	84.0	14	87.5	35	85.4
Underemployed	4	16.0	2	12.5	6	14.6
Number of Competitive Jobs Held in the Last 3 Years						
Zero	12	48.0	8	50.0	20	48.8
One	4	16.0	5	31.3	9	22.0
Two	6	24.0	–	–	6	14.6
Three or more	3	12.0	3	18.8	6	14.6
Financial Dependents						
Zero	3	12.0	1	6.3	4	9.8
One	10	40.0	9	56.3	19	46.3
Two	5	20.0	5	31.3	10	24.4
Housing						
Single-family Home	6	24.0	4	25.0	10	24.4
Mobile Home	1	4.0	1	6.3	2	4.9
Apartment or Condominium	5	20.0	2	12.5	7	17.1
Renting Room	3	12.0	1	6.2	4	9.8
Transitional housing	3	12.0	3	18.7	6	14.6
Homeless shelter	3	12.0	4	25.0	7	17.1
Motel	1	4.0	–	–	1	2.4
Residential Treatment	3	12.0	1	6.3	4	9.8
Locality						
Urban	19	76.0	13	81.3	32	78.0
Rural	4	16.0	3	18.8	7	17.1
No response	2	8.0	–	–	2	4.9

*SSI* Social Security Income, *SSDI* Social Security Disability Income, *SC* Service-Connected

**Table 3 Tab3:** Baseline Opioid Use and Treatment History

Variable	IPS (*N* = 25)		Non-IPS-VR (*N* = 16)		Total (*N* = 41)	
	*M*	*SD*	*M*	*SD*	*M*	*SD*
Duration of OUD (years)	10.2	7.9	10.4	12.7	10.3	9.8
	Frequency	Percent	Frequency	Percent	Frequency	Percent
Types of Opioids Used						
Prescription pain pills	19	76.0	11	68.8	30	73.2
Street-derived pills	10	40.0	8	50.0	18	43.9
Street-derived IV, not heroin	2	8.0	1	6.3	3	7.3
Heroin	8	32.0	5	31.3	13	31.7
Current OUD Treatment (past 12 months)						
Any Treatment	21	84.0	10	62.5	31	75.6
Medications for OUD	12	48.0	4	25	16	39.0
Other psychotropic medication	3	12.0	1	6.3	4	9.8
Supportive group therapy	9	36.0	3	18.8	12	29.3
Supportive individual therapy	8	32.0	7	43.8	15	36.6
Complimentary	3	12.0	1	6.3	4	9.8
Inpatient	1	4.0	2	12.5	3	7.3
Residential	5	20.0	5	31.3	10	24.3
Outpatient	2	8.0	2	12.5	4	9.8
OUD Treatment prior to 12 months						
Any Treatment	18	72.0	9	56.3	27	65.8
Medications for OUD	9	36.0	6	37.5	15	36.6
Other psychotropic medication	2	8.0	1	6.3	3	7.3
Supportive group therapy	8	32.0	6	37.5	14	34.1
Supportive individual therapy	8	32.0	8	50.0	16	39.0
Complimentary	1	4.0	3	18.8	4	9.8
Inpatient	6	24.0	4	25.0	10	24.4
Residential	5	20.0	4	25.0	9	22.0
Outpatient	2	8.0	–	–	2	4.8
MINI International Neuropsychiatric Interview						
Major Depressive (current)	3	12.0	1	6.3	4	9.8

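### The design overview says those randomised are in treatment for OUD, but eligibility does not require it and about a quarter enrolled had no OUD treatment in the past year

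*Protocol article*

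**What the plan says.** All references are to the Protocol article.

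- **Overview of design, aims, and hypotheses.** Consenting, eligible veterans "who are currently unemployed or under-employed and are in treatment for OUD are randomized to either IPS or non-IPS-VR". The final aim in the same section covers MOUD adherence, limited to veterans on MOUD, and OUD relapse, with no such limit.
- **Eligibility criteria.** The fourth inclusion criterion is that participants "have a history of current or lifetime OUD according to DSM-5". None of the four inclusion or six exclusion criteria refers to OUD treatment.
- **Recruitment procedures.** Besides clinical programmes, the trial takes veterans from vocational rehabilitation services and those who "are referred to the study, respond to the IRB-approved advertisement/letter, or make personal inquiry into the study". These routes do not imply OUD treatment.
- **Discussion.** The sample is described by current or lifetime OUD, with no treatment condition.
- **Results, Table 3.** Under the block headed "Current OUD Treatment (past 12 months" (closing bracket cut off), the first row reads "Any Treatment 21 84.0 10 62.5 31 75.6" and the MOUD row "Medications for OUD 12 48.0 4 25 16 39.0" (count and percent for IPS, non-IPS-VR and total).
- **MOUD outcome assessment.** Type of MOUD is to be controlled for in all statistical models.

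**The concern.** The article gives two descriptions of who is randomised, and they cannot both be right. If OUD treatment is a condition of entry, the eligibility list leaves it out and some enrolled veterans appear not to meet it. If it is not a condition, the overview misdescribes the trial. The gap cannot be put down to condensing a longer protocol, because the article states both versions.

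Two things are at stake.

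- **The population.** A report that took its population from the overview would attribute the effect on weeks worked, and any effect on relapse, to veterans in OUD treatment. A sizeable minority of the sample does not fit that label.
- **The relapse analysis.** It covers everyone and counts opioid misuse at least 4 times a month. Veterans under treatment and veterans with only a past disorder and no treatment may have quite different relapse risks. The one treatment-related covariate that the article names, MOUD type, does not distinguish veterans treated without medication from veterans with no treatment.

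**Working it through.** **Inputs.** Enrolment is from Results: "41 participants have been enrolled and randomized with 25 participants randomized to IPS", and the other 16 to non-IPS-VR. Treatment counts are from Table 3: any OUD treatment 21 (IPS) and 10 (non-IPS-VR), total 31; MOUD 12 and 4, total 16. The target of 120 randomised is from Primary outcome analysis.

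**1. Reproduce the table.** 31/41 = 75.6% and 16/41 = 39.0%, both as printed.

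**2. No OUD treatment in the past 12 months.** 41 − 31 = 10, and 10/41 = 24.4%. By arm this is 25 − 21 = 4 and 16 − 10 = 6.

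Wilson 95% interval with p = 0.2439, n = 41, z = 1.96:

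- Centre: (p + z²/2n) / (1 + z²/n) = (0.2439 + 0.0468) / 1.0937 = 0.266
- Half-width: 1.96 × √(p(1 − p)/n + z²/4n²) / 1.0937 = 1.96 × √(0.00450 + 0.00057) / 1.0937 = 0.128
- Interval: 0.138 to 0.393, or about 14% to 39%

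The exact (Clopper-Pearson) interval is 12.4% to 40.3%, so the choice of method does not matter.

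**3. Why 24% is a minimum.** Anyone in OUD treatment at baseline also had treatment within the past 12 months. The reverse need not hold, since a veteran treated ten months ago may have stopped. The share not in treatment at randomisation is therefore at least 10/41. This assumes that the 10 not counted are true negatives; Table 3 shows no separate row for missing answers on this item.

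**4. Carried to full enrolment.** If the share holds, 120 × 10/41 = 29.3, about 29 veterans. Across the Wilson interval, 120 × 0.138 to 120 × 0.393 gives about 17 to 47.

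**5. What MOUD type can and cannot separate.** Veterans without MOUD: 41 − 16 = 25. Of these, 31 − 16 = 15 had some other OUD treatment and 10 had none. This assumes that everyone counted under MOUD is also counted under any treatment. Even if MOUD type is coded with a level for none, that level pools 15 treated with 10 untreated veterans (60% and 40% of the 25).

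**The case against.** The strongest reply is that this is one loose clause. The abstract, the introduction and the opening of the overview speak simply of veterans with OUD, the Discussion gives the broader definition, and Table 3 publishes the treatment rates. A careful author would probably report the right population anyway. That limits the size of the point, but the overview clause remains wrong as written.

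A reader might also infer several stronger things that the article does not support.

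- **That the treatment aims do not fit the sample.** The adherence hypothesis is confined to veterans on MOUD, so untreated veterans do not enter it. Relapse as defined can be measured in anyone with a history of OUD. Neither aim is contradicted.
- **That the arms are confounded by treatment status.** Past-year treatment is 84.0% against 62.5%, a difference of 21.5 points. This comes from 41 of 120 participants under random allocation, with Fisher p = 0.15 and a 95% interval (Newcombe) of about −5 to +47 points. It is compatible with chance and may shrink, so it is no ground for choosing a covariate.
- **That IPS loses its integration component in untreated veterans.** The component is described as "closely integrated with the treatment team, in this case the outpatient substance use treatment or MOUD program". Table 3 counts OUD treatment only. A veteran without it may still have another substance-use or mental health team, or may enter treatment later.
- **That current and lifetime-only OUD should be separated in the models.** The MINI is used to confirm the diagnosis, but the article does not say that the two are recorded separately.
- **That effects should be reported for those in treatment at entry.** The tabulated variable covers 12 months and does not identify that group.

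The missing covariate is not in itself an error either, since covariate lists are commonly left to an analysis plan that is not shown. Adding past-year treatment is justified on a narrower ground: the article names MOUD type as the treatment-related control, and the counts show that it does not capture treatment.

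**Conclusion.** The point holds as an error in the stated population. The overview describes veterans in OUD treatment. The eligibility criteria, the recruitment routes and the Discussion describe veterans with current or lifetime OUD, treated or not. To date 10 of 41 (24%, 95% CI about 14% to 39%) had no OUD treatment in the past year, and the share not in treatment at randomisation is at least that if the 10 are true negatives. The figures are interim and the final share may differ.

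The comparison of weeks worked between arms is valid for whoever is enrolled, so there is no claim of bias in the primary analysis. The consequences are confined to whom the primary and relapse results are said to describe, and to a relapse model whose named treatment covariate pools two different groups of veterans without MOUD.

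**What to change.** 1. Reconcile the design overview with the eligibility criteria so that both state the population actually enrolled: veterans with current or lifetime OUD, with or without current OUD treatment. Word the primary and relapse conclusions for that population.
2. In the relapse model, add any OUD treatment in the past 12 months (yes/no) as a baseline covariate alongside MOUD type. Clinical assessments lists past and current OUD treatment among the baseline items, and Table 3 already tabulates this variable. The article reports no outcomes yet, so the change can be fixed before they are analysed.

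The first change costs only wording, at the price of a less specific headline population. The second costs one more covariate and needs no new data. Neither alters randomisation, eligibility in practice or data collection.
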